## Abstract

**Background:**

Cardiac rehabilitation in patients with chronic heart failure (CHF) has favourable effects on exercise capacity, the risk at hospital (re-)admission and quality of life. Although cardiac rehabilitation is generally recommended it is still under-utilised in daily clinical practice, particularly in frail elderly patients after hospital admission, mainly due to low referral and patient-related barriers. Cardiac telerehabilitation (CTR) has the potential to partially solve these barriers. The purpose of this study is to evaluate the effects of CTR as compared to standard remote care after hospital admission on physical functional capacity in CHF patients.

**Methods:**

In this randomised controlled trial, 64 CHF patients will be recruited during hospitalisation for acute decompensated heart failure, and randomised to CTR combined with remote patient management (RPM) or RPM alone (1:1). All participants will start with RPM after hospital discharge for early detection of deterioration, and will be up titrated to optimal medical therapy before being randomised. CTR will start after randomisation and consists of an 18-week multidisciplinary programme with exercise training by physical and occupational therapists, supported by a (remote) technology-assisted dietary intervention and mental health guiding by a physiologist. The training programme consists of three centre-based and two home-based video exercise training sessions followed by weekly video coaching. The mental health and dietary programme are executed using individual and group video sessions. A wrist-worn device enables remote coaching by the physical therapist. The web application is used for promoting self-management by the following modules: 1) goal setting, 2) progress tracking, 3) education, and 4) video and chat communication. The primary outcome measure is physical functional capacity evaluated by the Short Physical Performance Battery (SPPB) score. Secondary outcome measures include frailty scoring, recovery after submaximal exercise, subjective health status, compliance and acceptance to the rehabilitation programme, and readmission rate.

**Discussion:**

The Tele-ADHF trial is the first prospective randomised controlled trial designed for evaluating the effects of a comprehensive combined RPM and CTR programme in recently hospitalised CHF patients. We hypothesize that this intervention has superior effects on physical functional capacity than RPM alone.

**Trial registration:**

Netherlands Trial Registry (NTR) NL9619, registered 21 July 2021.

## Background

Heart failure (HF) is one of the leading causes of hospitalisations, morbidity and mortality worldwide [1, 2]. Heart failure hospitalisation leads to physical and physiological deconditioning, and the readmission rate is high (approximately 22–30%) in the first weeks after discharge [3–6]. Analogous to deconditioning, the frailty rate in the HF population is significant, with prevalence rates over 70% in hospitalised HF patients [7]. Frailty is a clinical syndrome characterised by a decline in physiological reserve and increased vulnerability, initiated by illness and/or ageing. HF, deconditioning and frailty frequently co-exist and are each independently predictors of mortality, disability and hospitalisation [8]. The high hospitalisation, morbidity and mortality rates in HF constitute to an extensive economic burden for healthcare systems.

Cardiac rehabilitation (CR) is an essential part of care for chronic heart failure (CHF) patients to improve health outcomes including quality of life, exercise capacity, and HF-related hospitalisations [9–15]. Current international guidelines recommend multidisciplinary HF management, exercise training (Class I, Level A evidence), and the consideration of home telemonitoring (Class IIb, Level B evidence) for all CHF patients regardless of HF aetiology [16–18]. Despite guideline recommendations, HF patients rarely participate in comprehensive CR programmes and the adherence rate during these programmes is low (approximately only 40% follows the exercise recommendations) [10, 17, 18]. As demonstrated by the HF-Action trial, low adherence rates are independently associated with cardiovascular mortality or HF hospitalisation [19, 20]. Causes of low referral and adherence rates are multifactorial and are determined by system-, professional-, patient-, and disease-related barriers [21, 22]. Examples of system-related barriers are limited CR facilities and lack of reimbursement for CR, and professional-related barriers are lack of endorsement for CR (possibly caused by lack of awareness for the benefits associated with CR participation). Patient-related barriers, such as logistic concerns (e.g. lack of transport), psychological status (e.g. motivation, depression, and anxiety) and socio-economic status, and disease-related barriers as recurrent episodes of decompensated HF and high disability burden in elderly patients are considered to play an even more important role [3, 9, 10, 23–25]. Yet, despite the fact that preliminary analyses showed that benefits of CR are particularly high in this frail elderly population [26], previous CR meta-analyses often excluded recently hospitalised CHF patients and had a relatively low median age (63 years in CR meta-analysis vs. 77 years Danish epidemiological HF-study) [12, 27]. The EJECTION-HF and REHAB-HF trials were the first to show that CR in recently hospitalised CHF patients is feasible and safe. However, a reduction in death or readmission rate could not be demonstrated and adherence to these centre-based CR interventions was poor [4–6]. Remote CR has the potential to help overcome barriers as low adherence and limited involvement of frail elderly in centre-based CR, and will therefore further improve health outcomes.

In the last decade, cardiac telerehabilitation (CTR) has emerged as a safe and effective alternative to centre-based CR for patients with coronary heart disease [28]. Although evidence on the effectiveness of CTR in CHF patients is less abundant, it has the same beneficial effects on quality of life in stable CHF patients as centre-based CR and is superior to no CR on improving functional capacity [29, 30]. Furthermore, in an exploratory study we confirmed that, even in a high-risk elderly population with combined CHF and chronic pulmonary disease, a CTR programme was feasible [31]. Conditions for such a CTR programme to be successful include a patient-centred design including elements for lifestyle and psychosocial guidance, prevention of disease progression, symptom control, and self-management [16]. These elements could be integrated in a non-invasive telemonitoring care pathway (remote patient management; RPM), using wearables, telephone support and a digital platform for early recognition of HF deterioration to reduce the risk for acute decompensated heart failure (ADHF) episodes, recurrent hospitalisations and cardiovascular death [16, 32]. The combination of multidisciplinary HF management, CTR and RPM improves the access to health care (by transferring care to patients’ home environments) and allows care to be adjusted to disease fluctuations while meeting the preferences and needs of individual patients, thereby improving utilisation, adherence, physical functional capacity and health outcomes.

In this study we aim to evaluate the effect of a comprehensive CTR programme combined with RPM in recently hospitalized CHF patients on physical functional capacity. We hypothesize that this intervention has superior effects on the physical functional capacity as compared to RPM alone.

## Methods

### Study design

This study is designed as a randomised controlled trial to evaluate the effect of CTR integrated with an RPM programme compared to RPM without CTR in CHF patients. Participants will be recruited during hospitalisation for ADHF at Máxima Medical Centre, Eindhoven/Veldhoven, and Catharina Hospital, Eindhoven, The Netherlands. Following hospital discharge, all participants will start with RPM and will be followed by their cardiologist and specialised HF nurse for up-titration to optimal medical therapy (OMT). When a stable situation is achieved (defined as OMT and unchanged HF symptoms for at least two weeks), participants will be randomised to either 18 weeks of comprehensive CTR in addition to RPM (intervention group), or RPM without CTR (control group). The period until reaching stable HF is at least 2 weeks after hospital discharge, and will be variable for all participants. All participants will sign informed consent before enrolment. Data will be collected at enrolment (-t_2_), during the pre-intervention period (hospital discharge until stable HF; -t_1_), at randomisation (t_0_), 18 weeks after randomisation (t_1_), and 6 months after randomisation (t_2_) (Fig. 1, Table 1). The study protocol was approved by the local Medical Research Ethics Committee (MREC) of Máxima Medical Centre. The trial is registered at the Netherlands Trial Register (NTR) with registration number Trial NL9619.

**Fig. 1 Fig1:**
[figure not shown]
Study design diagram. -t_2_ = at hospitalisation for acute decompensated heart failure, -t_1_ = after hospital discharge until stable heart failure is reached, t_0_ = randomisation and allocation, t_1_ = follow-up visit 1 – 18 weeks after randomisation, t_2_ = follow-up visit 2 – 6 months after randomisation

**Table 1 Tab1:**
[figure not shown]
Overview of the assessments during the study period

*-t*_*2*_ at hospitalisation for acute decompensated heart failure, *-t*_*1*_ within 2 weeks after hospital discharge, *t*_*0*_ randomisation and allocation, *t*_*x*_ intervention period, *t*_*1*_ follow-up visit 1 – 18 weeks after the intervention started, *t*_*2*_ follow-up visit 2 – 6 months after the intervention started

*Functional test*: CLET recovery = recovery of the constant-load exercise test, CPET max = maximal cardiopulmonary exercise test, HGS = Handgrip Strength test, PHB = wrist worn device ‘Philips Health Band’, SPPB = Short Physical Performance Battery

*Questionnaire*: Acceptance & satisfaction = questionnaire for acceptance and satisfaction of the CTR programme and digital platform, Activity level = subjective activity level question, DS-14 = Type D personality scale, EHFScBS = European Heart Failure Self-Care Behavior Scale, FitMáx = FitMáx©-questionnaire, GAD-7 = Generalised Anxiety Disorder assessment, HADS = Hospital Anxiety and Depression Scale, IPQ = Illness Perception Questionnaire, KCCQ-12 = Kansas City Cardiomyopathy Questionnaire, MLHFQ = Minnesota Living with Heart Failure Questionnaire, MMAS-8 = adjusted Morisky Medication Adherence Scale, MoCA = Montreal Cognitive Assessment, NutriMáx = nutrition questionnaire based on the national nutrition guideline from the Dutch Health Council, PLF = Premorbid Lifestyle questionnaire, PHQ-9 = Patient Health Questionnaire, SNAQ = Short Nutritional Assessment Questionnaire

*Other*: Laboratory measurements (e.g. NTproBNP, GDF15)

^a^All objectives will be assessed in both groups

### Study population

All patients currently hospitalised for ADHF will be screened for study participation according to the in- and exclusion criteria (Table 2). Patients who are interested will be enrolled before discharge after signing informed consent.

**Table 2 Tab2:** Inclusion and exclusion criteria

Inclusion criteria:
1) Aged ≥ 18 years
2) Diagnosed with congestive heart failure
3) Hospitalised primarily for acute decompensated heart failure (ADHF) at the time of inclusion
4) Sufficient digital literacy, or caretaker with digital literacy
5) Able to speak and read the Dutch Language
Exclusion criteria:
1) Unable to understand the purpose and procedures of the study
2) Unable to walk a distance of 4 m independently (walking aids are allowed)
3) Cardiac rehabilitation programme followed in the previous 12 months
4) No internet connection
5) Untreated life-threatening cardiac arrhythmia
6) Early phase after acute coronary syndrome (latest 3 months)
7) Uncontrolled hypertension
8) Advanced atrioventricular block
9) Severe aortic stenosis
10) Up-coming major (cardiac) surgery in 3 months

### Randomisation, blinding and treatment allocation

Participants are randomly allocated to the intervention or control group (1:1) after reaching stable HF and completing the first measurements. Participants will be replaced when discontinuing from study protocol before randomisation. Randomisation is performed by the investigator using a computerised randomisation system in the web-based database software Castor EDC (Castor Electronic Data Capture, Ciwit BV, Amsterdam, The Netherlands). The computer system uses variable block sizes (2,4) stratified for age (< 75 years or ≥ 75 years) and left ventricular ejection fraction (LVEF ≤ 40%, LVEF 41 – 49% or LVEF ≥ 50%) for randomisation. Overall, patients with HF are elderly with an average age of 75.2 years in Western Countries as presented by Norhammar et al. [33]. The participants, investigator, and other medical professionals will not be blinded for the treatment allocation due to the nature of the intervention. For the assessment of the functional tests (Short Physical Performance Battery and Handgrip Strength test) a blinded investigator will be involved.

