### Statistical analysis

All analyses will be performed according the intention-to-treat principle. Descriptive statistics will be used to present demographic and baseline characteristics. Between- group differences in the primary and secondary endpoints will be analysed by the unpaired T-test for continuous variables and by a chi squared test for categorical variables. A paired T-test will be used to evaluate within-group differences for the primary endpoint.

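### Hospital is neither a randomisation stratum nor an analysis term in this two-hospital trial; the planned tests stay valid, and pre-specifying a hospital term is a cheap, optional gain in precision

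*Protocol article*

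**What the plan says.** Study design names two sites: "Participants will be recruited during hospitalisation for ADHF at Máxima Medical Centre, Eindhoven/Veldhoven, and Catharina Hospital, Eindhoven, The Netherlands".

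Randomisation, blinding and treatment allocation describes a 1:1 allocation: "The computer system uses variable block sizes (2,4) stratified for age" (two levels) "and left ventricular ejection fraction" (three levels). That makes six strata, and hospital is not among them.

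Statistical analysis fixes the between-group tests for every endpoint: "differences in the primary and secondary endpoints will be analysed by the unpaired T-test for continuous variables", and a chi-squared test for categorical ones. For change within arms it adds: "A paired T-test will be used to evaluate within-group differences for the primary endpoint". None of these tests has a place for hospital.

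**The concern.** Hospital could plausibly relate to outcome here. Nurses and cardiologists review alerts, adjust medication and decide on action in both arms (Remote patient management). The intake and first three training sessions of the intervention take place in hospital (Physical training). Readmission means a hospitalisation of at least 24 h (Readmission rate and other adverse events), so it depends partly on local admission practice. Balancing age and LVEF does not balance these things.

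An unadjusted mean difference carries the chance imbalance in hospital share, multiplied by the outcome difference between hospitals, in full. With 64 patients that imbalance need not be trivial. Adding hospital after an imbalance has been seen, in a trial where investigators know the allocation, would look data-driven. If hospital is to be used, it should be named beforehand.

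**Working it through.** **The plan's own figure.** Sample size calculation gives an effect of 1.6 points, SD 2.17, N = 64 and power 0.80. Alpha is not stated, so I assume two-sided 0.05. Per arm, 2 x (1.96 + 0.8416)^2 x 2.17^2 / 1.6^2 = 28.9, so 29 per arm and 58 in total; the exact t-test needs 30 per arm, 60 in total. At 32 per arm the t-test has power 0.827. The stated 64 is slightly more than needed, which would fit an unstated dropout allowance (60/0.95 = 63.2, rounded up to 64). This has no bearing on hospital.

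**Inputs not in the article (assumed).** Share of patients at the larger hospital: 0.5 to 0.8. Difference in mean SPPB between hospitals: 0.5, 1.0 and 1.5 points. Proportions in the six strata: also assumed.

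**Step 1: chance imbalance.** The arm difference in hospital share has SD = sqrt(4p(1-p)/64), which is 0.125 at p = 0.5 and 0.100 at p = 0.8. Simulating blocks of 2 and 4 in six strata, 20,000 trials per setting, gives mean imbalance about 0, SD 0.126 and 0.100, and 95% limits of 0.25 and 0.20.

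**Step 2: shift in the estimate.** Shift = imbalance x hospital gap. The smallest value at the 95% limit is 0.20 x 0.5 = 0.10; the largest is 0.25 x 1.5 = 0.375. For a gap of 1.0 it is 0.20-0.25. The standard error is 2.17 x sqrt(2/32) = 0.5425, so a 1-point gap gives a shift of less than half a standard error.

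**Step 3: validity over all trials.** I simulated whole trials with total SD 2.17, hospital shares 0.5, 0.65 and 0.8, and all three gaps. The false-positive rate of the unadjusted t-test was 0.048-0.052 in every setting.

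**Step 4: the tail trial.** Take 20 of 32 patients from one hospital in one arm and 12 of 32 in the other, an imbalance of 8/32 = 0.25. Ranges cover 2.17 read as the total or as the within-hospital SD.

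| Hospital gap | Shift | Conditional false-positive rate | Power, adverse shift | Power, favourable shift |
|---|---|---|---|---|
| 0.5 | 0.125 | 0.054 | 0.76-0.77 | 0.88 |
| 1.0 | 0.25 | 0.067-0.069 | 0.67-0.69 | 0.91-0.92 |
| 1.5 | 0.375 | 0.086-0.091 | 0.56-0.61 | 0.93-0.96 |

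**Step 5: average gain from a hospital term** (total SD 2.17, the three hospital shares).

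| Hospital gap | Power, unadjusted | Power, adjusted |
|---|---|---|
| 0.5 | 0.82-0.83 | 0.82-0.83 |
| 1.0 | 0.82-0.83 | 0.83-0.84 |
| 1.5 | 0.82-0.83 | 0.85-0.87 |

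**Step 6: break-even.** The variance that hospital explains, relative to 2.17^2 = 4.709, is d^2 x p(1-p) / 4.709. This is 0.8% at d = 0.5, p = 0.8 and 11.9% at d = 1.5, p = 0.5. The term costs about 1/62 = 1.6% in variance. The two are equal at d = 0.55 when p = 0.5, and at d = 0.69 when p = 0.8.

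**The case against.** Nothing in the planned test is wrong. Any unadjusted comparison omits baseline variables, the expected imbalance is zero, and step 3 confirms that the test keeps its level. That stands.

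The hospital gap is an assumption. The article reports no difference, and some of its text points to similarity: both hospitals are in the Eindhoven area, with common eligibility criteria, one monitoring platform, guideline-based up-titration and the same stability requirement before randomisation. A gap of 1.0 point is large beside the 0.4-1.5 points that the article cites as a better functional capacity. A case-mix difference in SPPB would also largely show in SPPB at randomisation, so adjusting for that would capture part of it. All this stands, and it lowers the priority.

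A journal article condenses the full protocol, and centre adjustment is often left to the analysis plan. This carries less weight here, because the section does not defer the method: it names unadjusted tests for all endpoints. A hospital term would change a stated method.

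A reader might infer that ignoring hospital biases the trial, or that it inflates false positives and cuts power in general. The article does not support that. The step 4 figures describe a tail of roughly 5% of trials at an even hospital split. The adverse direction is about half of that tail, and the mirror-image trial gains power. Feeding SD 2.17 and a 0.25-point shift into a noncentral t gives 0.074 for a 1-point gap. That is too high, because the hospital difference also widens the SD that the t-test pools; the direct simulation gives about 0.067.

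**Conclusion.** The point holds as an optional improvement. Two hospitals recruit, and hospital enters neither the strata nor the stated tests. The result is chance imprecision: the planned comparison is unbiased over randomisations, with a false-positive rate of about 0.05.

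In an unlucky trial, a hospital-share imbalance of up to 0.20-0.25 moves the SPPB difference by about 0.1-0.4 points, with a conditional false-positive rate of about 0.05-0.09. On average, adjusting gains about 0-1 percentage point of power for gaps up to 1.0 point and 2-4 at 1.5. At gaps of about 0.5 points or less there is no net gain.

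These figures rest on assumed hospital shares, stratum proportions and hospital gaps, and on two-sided alpha 0.05. For readmission the article gives nothing from which to size the effect.

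**What to change.** In Statistical analysis, pre-specify recruiting hospital (two levels) as a fixed effect in the between-arm model for SPPB and the continuous secondary endpoints, alongside any other baseline adjustment. For categorical endpoints such as readmission, use a comparison stratified by hospital, for example Cochran-Mantel-Haenszel.

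Leave the randomisation unchanged. Adding hospital would double the six strata to twelve, about five patients each (64/12 = 5.3), with many incomplete blocks.

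The cost is one or two sentences and one degree of freedom. Recruiting hospital is known for each patient, since enrolment takes place during admission. If the hospitals do not differ, the loss of precision is under 2%.

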### Remote patient management

Directly after hospital discharge, study participants start with remote patient management (RPM). RPM, also known as telemonitoring, allows health care providers to closely review patient-generated health data, interact with the patient, and initiate clinical treatment if needed [34]. RPM is associated with reduced mortality, and admission rate [32]. Study participants are asked to daily measure their vital parameters (e.g., heart rate, blood pressure) and weight with medical devices (iHealth Track Blood Pressure monitor, iHealth Lina scale) and manually entry the data on the digital monitoring platform (Mibida BV). In addition to the vital parameters, participants are instructed to answer 5 short HF related questions on the platform (e.g., ‘Do you experience shortness of breath?’). Alerts will be generated by the platform based on predefined and individualised reference values. A specialised cardiac nurse will review the patient-generated health data and alerts during the weekdays, and a cardiac care nurse from the Coronary Care Unit / Cardiology Ward will review the data during evenings and weekends. The patient is instructed to contact the nurse by telephone between defined hours when an alert is generated; for urgent matters the medical professionals are available 24/7. Besides daily monitoring to recognise early clinical decompensation, the specialised nurse and cardiologist are responsible for the up titration to optimal medical therapy (OMT) according to ESC guidelines [16]. In a daily meeting with the cardiologist, the nurse will discuss patients with clinically relevant alerts, patients for medication up titration, and patients for remote routine follow-up (2 weeks, and 6 weeks after hospital discharge, and every 3 months). The team will decide what action is needed (e.g. increase in diuretics because of weight gain and oedema). The specialised nurse and cardiologist are primarily responsible for achieving OMT after hospital discharge. All participants will continue with RPM during the entire study period.

### Intervention group: cardiac telerehabilitation

This multidisciplinary 18-weeks CTR programme includes interventions on physical function and activity, diet, and mental health. Physical, nutritional and psychological goals will be assessed by the specialised nurse at the CTR intake procedure. After the general intake, the patient will be referred for an intake with the physical and occupational therapist, dietician, and psychologist.

